## Abstract

**Background:**

Knee osteoarthritis (KOA) is a common degenerative joint disease that typically affects individuals over 40 years of age and is characterized by knee pain, stiffness, and functional impairment. Current treatment options, including basic care, pharmacologic therapy, and surgery, often provide limited pain relief or are associated with adverse effects, high costs, and surgical risks. Acupuncture has been conditionally recommended by international guidelines for KOA management and has shown beneficial effects in alleviating pain and improving function. However, most studies have investigated single modalities such as manual acupuncture or electroacupuncture, leaving opportunities to explore strategies that may further enhance therapeutic outcomes. Opposing needling, a classical technique involving contralateral point selection, has demonstrated superior analgesic effects in various chronic pain conditions and is increasingly applied in KOA.

**Methods:**

This two-center randomized controlled trial will enroll 108 eligible patients with KOA, who will be randomly assigned in a 1:1:1 ratio to opposing needling plus electroacupuncture, sham opposing needling plus electroacupuncture, or electroacupuncture alone. The 12-week study comprises an 8-week intervention period and a 4-week follow-up, with treatments administered three times per week. The primary outcome will be the Western Ontario and McMaster Universities Osteoarthritis Index (WOMAC), while secondary outcomes will include WOMAC subscales, Visual Analog Scale, Numeric Rating Scale, Global Pain Scale, Lequesne Index, Knee Injury and Osteoarthritis Outcome Score, and Short Form-36 Health Survey.

**Discussion:**

The findings are expected to provide robust evidence regarding the efficacy and safety of opposing needling as an adjunctive therapy for KOA and to inform optimized treatment strategies.

**Clinical trial registration:**

itmctr.ccebtcm.org.cn, ITMCTR2025001291.

## Introduction

1

Knee osteoarthritis (KOA) is a common chronic degenerative joint disorder predominantly affecting individuals over 40 years of age, characterized by progressive knee pain, stiffness, and functional impairment (1). It can lead to joint deformity and disability (2), imposing substantial burdens on patients, families, and healthcare systems. Current treatments, including basic care, pharmacologic therapy, and surgery (3), have limitations: basic interventions improve general condition but rarely relieve pain (3, 4); pharmacologic management may reduce inflammation and slow cartilage degeneration but carries risks such as nephrotoxicity and gastrointestinal or cardiovascular complications (5–8); surgical management is effective but costly and associated with postoperative pain, limited mobility, and prosthetic lifespan concerns (9). Thus, identifying effective, low-cost, and low-risk therapeutic strategies is essential for delaying disease progression and improving quality of life.

Acupuncture has demonstrated analgesic efficacy in chronic pain conditions and is conditionally recommended by clinical guidelines for KOA management, including the 2019 American College of Rheumatology (ACR) and Arthritis Foundation guideline (10). A systematic review indicated that acupuncture has both short-term and long-term efficacy in the treatment of KOA (11). Moreover, acupuncture has been recognized by the National Institutes of Health (NIH) as an important complementary and alternative therapy for KOA management (12). Electroacupuncture—a form of acupuncture combined with electrical stimulation—has been shown to promote cartilage repair and provide faster and superior pain relief compared with manual acupuncture (13–15). Multiple preclinical studies have shown that electroacupuncture can exert analgesic effects through various mechanisms (16), including the promotion of endogenous analgesic substance release (17), inhibition of pronociceptive mediator production (18), modulation of the MAPK signaling pathway (19), and suppression of pain sensitization (20).

Opposing needling, a classical technique involving contralateral acupoints with deep insertion along meridians, is primarily indicated for pain (21, 22) and has documented efficacy in various chronic pain disorders (23–27). From the perspective of traditional Chinese medicine, opposing needling emphasizes the concept of bodily integrity. When the flow of qi and blood along the meridians is obstructed and the left–right balance is disrupted, the meridian function on the affected side is weakened while the healthy side remains normal. Therefore, acupuncture at the corresponding points on the healthy side can stimulate the flow of qi, promote circulation of blood and qi, eliminate pathogenic factors, and restore the function of the affected meridians, achieving a dynamic balance of “yin and yang” between both sides of the body. From the perspective of modern medicine, studies have demonstrated that opposing needling can effectively relieve pain through protective inhibition of the cerebral cortex, reflex regulation via the nervous and humoral systems, and interruption of local nociceptive stimuli. The signals generated by acupuncture not only modulate pain transmission through spinal segmental connections but also promote the release of multiple endogenous analgesic substances, thereby increasing pain thresholds and activating descending inhibitory signals from higher centers. These combined effects contribute to the improvement of local pain and provide comprehensive pain management (28).

Previous studies suggest that opposing needling may enhance therapeutic outcomes in KOA, either alone or combined with other treatments (29–32). This indicates that opposing needling not only exerts an independent analgesic effect but may also play an adjunctive role. Therefore, we propose a reasonable hypothesis that combining opposing needling with electroacupuncture may produce additive or synergistic analgesic effects based on the analgesic action of electroacupuncture.

Given the independent and potential synergistic effects of opposing needling, we designed a sham-controlled, two-center randomized trial to evaluate the efficacy and safety of opposing needling as an adjunct to electroacupuncture in KOA patients. The study implements improved control procedures, comprehensive outcome measures, and refined group allocation to provide robust evidence and novel insights for clinical management.

## Methods

2

### Trial design

2.1

This is a three-armed RCT conducted at the Rehabilitation Department of the Thirteenth People’s Hospital of Chongqing and the Rehabilitation Department of Chengdu Pidu District Traditional Chinese Medicine Hospital. The total duration of the trial will be 12 weeks, comprising an 8-week intervention period followed by a 4-week follow-up period. A flow chart of the clinical trial procedure is presented in Figure 1, and the schedule of outcome measurements is detailed in Supplementary File 1 and Table 1.

**Figure 1 fig1:**
[figure not shown]
Flow chart for clinical trial procedure.

**Table 1 tab1:** Schedule of outcome measurements.

Study period	Baseline	Treatment	End of treatment	Follow-up
Assessment point/time	0 weeks/1st	4 weeks/2nd	8 weeks/3rd	12 weeks/4th
Diagnosis and treatment				
Current/past medical history	×			
Physical examination	×			
Knee X-ray	×			
Informed consent	×			
Specialist assessment				
WOMAC	×	×	×	×
VAS	×	×	×	
NRS	×	×	×	×
GPS	×	×	×	
Lequesne	×	×	×	
KOOS	×	×	×	
SF-36	×	×	×	×
Trial assessment				
Adverse event assessment			×	
compliance assessment			×	
Clinical trial completion			×	
security assessment			×	
Post-completion work on test cases				
The person in charge reviews the case	Observations are reviewed and signed by the person in charge within 1 week of the end of the observation and entered into the electronic database.			
Review of medical cases by the Ombudsman	Regular monitoring and auditing by subject matter ombudsmen			

### Participants

2.2

#### Recruitment

2.2.1

Participants will be recruited from the outpatient clinic of the Rehabilitation Department at Thirteenth People’s Hospital of Chongqing and the Rehabilitation Department at Chengdu Pidu District Traditional Chinese Medicine Hospital, as well as through offline recruitment posters and online social media platforms.

#### Diagnostic criteria for KOA

2.2.2

Only patients who meet the diagnostic criteria for KOA (based on the 1995 American College of Rheumatology classification criteria) will be eligible for inclusion in this study. Patients must have experienced recurrent knee pain within the past month and meet at least two of the following four criteria:– Age ≥40 years;– Morning stiffness ≤30 min;– Crepitus on motion;– Radiographic evidence on standing or weight-bearing X-rays demonstrating joint space narrowing, subchondral sclerosis and/or cystic changes, and osteophyte formation at the joint margins.

#### Inclusion criteria

2.2.3

Only patients who meet all of the following five criteria will be eligible for inclusion in this study:– Diagnosed with KOA according to the specified diagnostic criteria;– Age ≥40 years, with knee pain persisting for at least 6 months;– Radiographic evidence of Kellgren–Lawrence Grade II or III KOA (Grade II: definite osteophyte formation with possible joint space narrowing; Grade III: moderate osteophyte formation with definite joint space narrowing and subchondral sclerosis);– NRS pain score ≥4 within the past week (scale from 0 to 10, with higher scores indicating more severe pain);– Willingness to participate in the study and provide written informed consent.

#### Exclusion criteria

2.2.4

Participants will be excluded if they meet any of the following criteria:– Significant inflammatory response in the affected knee, such as visible swelling or moderate to large joint effusion;– Knee pain caused by other diseases, including but not limited to rheumatoid arthritis or infectious arthritis;– History of knee joint replacement surgery, or scheduled for joint replacement during the study period;– Arthroscopic surgery within the past 12 months or intra-articular injection within the past 6 months;– Receipt of acupuncture treatments within the past 3 months;– Presence of severe acute or chronic organic diseases or psychiatric disorders, such as heart failure, severe arrhythmias, angina pectoris, renal failure, hepatic failure, malignancies, chronic obstructive pulmonary disease (COPD), dementia, or schizophrenia;– Coagulation disorders or presence of implanted metal devices (e.g., cardiac pacemakers, deep brain stimulators);– Needle phobia or known allergy to metal;– Pregnant or breastfeeding women;– Participation in another clinical trial within the past 3 months or currently enrolled in another trial.

#### Withdrawal/dropout criteria

2.2.5

– Participants who are unable to tolerate acupuncture or fail to adhere to the designated study protocol;– Participants who develop severe joint inflammation during the study, characterized by significant swelling or moderate to large joint effusion;– Participants who experience other medical conditions requiring hospitalization, such as acute myocardial infarction or ischemic stroke.

#### Management of withdrawal/dropout cases

2.2.6

– In the event of a participant dropout, the primary investigator should make efforts to contact the participant using methods such as home visits, phone calls, or letters to inquire about the reason for withdrawal. The date of the last treatment session should be recorded, and all feasible assessments should be completed.– For participants who withdraw due to adverse reactions or treatment failure, the primary investigator should provide appropriate treatment based on the participant’s specific condition.– Once a participant has been assigned a randomization number, they will be considered part of the study, regardless of subsequent changes in diagnosis or treatment completion.– All withdrawal/dropout cases will undergo intention-to-treat analysis after the study is completed.

### Sample size

2.3

The sample size was estimated based on preliminary data (33, 34). The mean and standard deviation (SD) of the change in total WOMAC score after 8 weeks of treatment were assumed to be −32.3 ± 1.15 in the opposing needling plus electroacupuncture group, −22.42 ± 2.32 in the sham opposing needling plus electroacupuncture group, and −8.87 ± 0.81 in the conventional electroacupuncture group. The test power (1 − *β*) was set at 0.9, and the significance level (*α*) was set at 0.05. Based on these parameters, 30 participants were required per group. Considering a 20% dropout rate, the final sample size was determined to be 36 participants per group, resulting in a total of 108 participants.

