### Randomization

2.4

Eligible participants will be randomly assigned in a 1:1:1 ratio to the opposing needling plus electroacupuncture (OE) group, sham opposing needling plus electroacupuncture (SE) group, or electroacupuncture alone (EA) group, according to the order of enrollment. The randomization sequence will be generated by an independent third party not involved in this study using SAS 9.4, with a stratified randomization method; the stratification factor is study center, and the block size is 6. Group allocation will be concealed in sequentially numbered, opaque, sealed envelopes. The envelopes will be opened by the acupuncturist immediately before the first treatment to determine group assignment.

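### The means and SDs printed in section 2.3 require about 3 participants per group, not 30, so the stated 30 and its 90% power do not follow from them

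*Protocol article*

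**What the plan says.** Protocol article, section 2.3 (Sample size), introduces its inputs with "The mean and standard deviation (SD) of the change in total WOMAC score after 8 weeks of treatment were assumed to be" and then lists three values, all reductions (the minus sign falls outside the quotes):

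- OE arm: "32.3 ± 1.15 in the opposing needling plus electroacupuncture group"
- SE arm: "22.42 ± 2.32 in the sham opposing needling plus electroacupuncture group"
- Electroacupuncture alone (EA): "8.87 ± 0.81 in the conventional electroacupuncture group"

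Power "was set at 0.9, and the significance level" "was set at 0.05". The section then draws its result directly from these figures: "Based on these parameters, 30 participants were required per group". An allowance for 20% dropout raises this to 36 per group, 108 in total. Section 2.4 (Randomization) confirms equal allocation: "Eligible participants will be randomly assigned in a 1:1:1 ratio". Section 2.7.1.1 makes the change from baseline to week 8 the focus of the primary analysis, so the sample size concerns the primary endpoint.

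**The concern.** The section prints both the inputs and the output and says that one gives the other. The mean changes lie 10 to 23 points apart, while the SDs are 0.81 to 2.32. With differences that large relative to the spread, a handful of patients would be enough. A requirement of 30 therefore signals that either the SDs or the 30 came from something other than what is printed.

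At stake is the justification for the size of the trial. If the spreads are wrong, the 90% has no stated basis, and a reader cannot tell what power 108 participants provide for the primary endpoint.

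**Working it through.** **Inputs.** All come from section 2.3, except the 1:1:1 ratio (section 2.4): means −32.3, −22.42 and −8.87; SDs 1.15, 2.32 and 0.81; alpha 0.05 (taken as two-sided); power 0.90.

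**Step 1. Attempt to reproduce 30, pairwise.** Average SD = √[(SD₁² + SD₂²)/2]; d = difference / average SD.

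| Pair | Difference | Average SD | d | n per group for 90%, t-test |
|---|---|---|---|---|
| OE vs SE | 9.88 | √[(1.3225 + 5.3824)/2] = 1.83 | 5.40 | 3 |
| SE vs EA | 13.55 | 1.74 | 7.80 | 2 (pooled) or 3 (Welch) |
| OE vs EA | 23.43 | 0.99 | 23.6 | 2 |

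For OE vs SE at n = 3, the noncentrality is 9.88 / (1.83 × √(2/3)) = 6.61, with 4 degrees of freedom and critical value 2.776. Pooled-t power is 99.7%. Because the SDs are unequal and n is tiny, I also simulated:

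| n per group | Pooled t, simulated | Welch, simulated |
|---|---|---|
| 2 | 78% | about 46% |
| 3 | 99.5% | about 95% |

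Two per group is too few and three is enough.

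**Step 2. Attempt to reproduce 30, three-group F-test.** The grand mean is −21.20, and the squared deviations of the arm means sum to 276.73. The SD of the means is √(276.73/3) = 9.60. The pooled within-group SD is √[(1.3225 + 5.3824 + 0.6561)/3] = 1.57, so f = 9.60/1.57 = 6.13. At n = 2 per group power exceeds 99.9%. With the largest SD (2.32) used for every arm it is still 99.8%.

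**Step 3. Other readings.** One-sided as well as two-sided tests were tried, at alpha 0.05, 0.025, 0.0167 and 0.01, with normal approximation, pooled t and Welch. The largest requirement for any pair was 4 per group. The stated 30 is not reproduced. On the printed inputs, 30 per group has power of essentially 100%, not 90%.

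**Step 4. Work backwards from 30.** With n = 30 per group, two-sided 0.05 and power 0.90, a t-test detects d = 0.851. The SD that makes 30 the right answer is then:

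- OE vs SE: 9.88/0.851 = 11.6, which is 11.6/1.83 = 6.3 times the printed average
- SE vs EA: 13.55/0.851 = 15.9
- OE vs EA: 23.43/0.851 = 27.5
- overall F-test: f = 0.382, so the SD is 9.60/0.382, about 25.2

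**Step 5. Sensitivity to the SD.** The documents give no other SD, so this range is assumed. Power for a 9.88-point OE vs SE difference, 30 evaluable per group, unadjusted two-sided t-test:

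| SD | Power |
|---|---|
| 10 | 0.96 |
| 11.6 | 0.90 |
| 15 | 0.71 |
| 20 | 0.47 |

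**The case against.** The strongest reply is that the error runs in the safe direction: on the printed inputs, 30 per group is about ten times what is needed. That is correct. A reader might infer from the mismatch that the trial is underpowered, and the documents do not support that. It would need a true SD well above 11.6 for OE vs SE, and no such figure is given. The lower powers in Step 5 rest on an assumed SD range and on one comparison, and they ignore the covariate adjustment planned in section 2.12. If the overall F-test was intended, 30 per group keeps 90% power up to an SD of about 25.2.

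A reader might also infer that the printed values are standard errors. This is plausible and could be harmless. If they came from about 40 patients per arm (assumed), the average SD for OE vs SE would be 1.83 × √40 = 11.6 and 30 would be right, with only the label wrong. From 30 per arm (assumed), the SDs would be 6.3, 12.7 and 4.4, and OE vs SE would need 23 per group. The source sample sizes are not given, so the point cannot be settled. The implausibility of the SDs is likewise a judgement, since the article gives no WOMAC scoring range or reference SD.

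Two further objections stand. A null result would not become uninterpretable, because it is read from the confidence interval and the observed SD. And a condensed article need not name the test, the comparison or the software, so I do not count their absence as a fault.

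None of this touches the core. The article prints inputs and result and says that one yields the other, and no standard comparison or test makes that true. A fuller document could supply different inputs but could not make the printed statement correct.

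**Conclusion.** The point holds as an error in a stated derivation. The printed means, SDs, alpha and power require 3 per group for the closest pair and 2 for the three-group F-test, against a stated 30. Neither the 30 nor the 90% follows from section 2.3. This conclusion uses only the printed figures and standard tests.

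The likely cause, SDs too small to be between-patient values, is a judgement. Whether the planned 108 are too few, enough or more than enough for OE vs SE cannot be determined from the documents. It turns on whether the true SD lies above or below about 11.6.

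**What to change.** Recheck the two preliminary sources cited in section 2.3 and establish whether the values after the ± signs are SDs or standard errors. Correct the SDs, or the derived 30 if the SDs prove right. Then restate the power that the planned 108 participants deliver with the corrected SD, and say which comparison that power refers to.

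If no reliable SD can be found, say so. State that 30 evaluable per group gives 90% power for a 9.88-point difference only if the SD is at most about 11.6, and show power over an openly assumed SD range, as in Step 5.

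The cost is one rewritten paragraph. No extra patients and no change of procedure are needed. The downside is that the stated power may become less favourable.

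### The 20% dropout allowance was added as 30 × 1.2, so 36 per group covers only 16.7% dropout (minor arithmetic correction)

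*Protocol article*

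**What the plan says.** The protocol article, section 2.3 (Sample size), gives three figures in sequence.

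- Base requirement: "Based on these parameters, 30 participants were required per group".
- Allowance for loss, which fixes the number to enrol: "Considering a 20% dropout rate, the final sample size was determined to be 36 participants per group".
- Total: 108 across the three arms.

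No inflation formula is shown. Power is taken as 0.9 and alpha as 0.05; neither the sidedness nor the test used for sizing is given. The assumed reductions in total WOMAC at 8 weeks (mean ± SD) are 32.3 ± 1.15 for the combined arm, 22.42 ± 2.32 for the sham arm and 8.87 ± 0.81 for electroacupuncture alone.

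Two other sections bear on the point. Section 2.2.6 asks for whatever assessments are feasible in dropouts and places all of them under intention-to-treat. Section 2.12 plans complete-case analysis when at most 5% of data are missing without a systematic pattern, and multiple imputation under missing at random otherwise. Neither revises the figures in section 2.3.

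**The concern.** A dropout rate is the fraction of enrolled participants who are lost. Section 2.2.6 fits that reading, since a participant belongs to the study once a randomization number has been assigned. The enrolled number must therefore be the required number divided by the retained fraction. Adding 20% of the required number gives a smaller figure, and the loss is then taken from the larger enrolled base. As printed, 30 required, 20% lost and 36 enrolled cannot all hold.

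What is at stake is whether the sample size keeps the margin that the protocol says it has. The figure is also one that readers will check the achieved retention against.

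**Working it through.** **Inputs (section 2.3):** required n = 30 per group; dropout d = 0.20; enrolled 36 per group, 108 in total.

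**1. The plan's own figure.** n × (1 + d) = 30 × 1.20 = 36 exactly, and 36 × 3 = 108. This reproduces the plan.

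**2. Inflation that matches a 20% loss of those enrolled.** n / (1 − d) = 30 / 0.80 = 37.5, rounded up to 38 per group; 38 × 3 = 114. Check: 38 × 0.80 = 30.4, which is at least 30.

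**3. What 36 per group delivers.**
- Remaining after a 20% loss: 36 × 0.80 = 28.8, that is 1.2 below 30.
- Dropout that 36 can absorb while keeping 30: (36 − 30)/36 = 16.7%.
- Enrolment gap: 38 − 36 = 2 per group; 114 − 108 = 6 in total, or 6/108 = 5.6%.

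**4. Does this cost power?** That depends on what the 30 represents.

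*(a) If 30 per group were exactly the 90% requirement* for a two-sided 0.05 comparison of two groups (normal approximation), the standardised difference would be (1.960 + 1.282)/√(30/2) = 0.837. Power at n per group is Φ(0.837 × √(n/2) − 1.960):

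| n per group | Power |
|---|---|
| 30 | 0.900 |
| 29 | 0.890 |
| 28.8 | 0.888 |
| 28 | 0.879 |

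The 0.837 is back-solved from the conclusion; the protocol does not contain it.

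*(b) On the inputs the protocol prints*, the smallest contrast is opposing needling against sham: 32.3 − 22.42 = 9.88. The pooled SD is √((1.15² + 2.32²)/2) = 1.83, so the standardised difference is 9.88/1.83 = 5.4. An exact t calculation (two-sided 0.05) gives power 0.77 at 2 per group and 0.997 at 3. A three-group ANOVA needs 2 per group. At 28.8 per group power is essentially 1.

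The base figure of 30 therefore does not follow from the printed means and SDs. With a difference of 9.88, an SD of about 9.88/0.837 = 11.8 would be needed to arrive at 30.

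**The case against.** Four points can be made for leaving the text alone.

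**Dropout is not the same as a missing outcome.** Sections 2.2.5, 2.9 and 2.10 count non-adherence, intolerance, emergency unblinding and receipt of other treatment as withdrawal or dropout. Section 2.2.6 asks for feasible assessments in such cases, so some dropouts may still give a week-8 WOMAC. This stands in part: 28.8 is what remains if all 20% give no week-8 outcome, and the true number could be higher. But section 2.3 takes no credit for this. It adds participants precisely because it treats dropout as a loss to be made good.

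**Intention-to-treat with multiple imputation keeps all 36 in the analysis.** It keeps them in the analysis set, but imputation does not restore the information in outcomes that were never observed. This does not rescue the allowance.

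**The shortfall is trivial.** It is small: 1.2 participants per group among those remaining. That is a reason to grade the point as minor, not to leave a wrong figure in print.

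**The base of 30 is itself not derivable.** This is true, and it is the larger weakness in the section. It limits what can be said about power, but it does not make the inflation step right: whatever base is finally justified, multiplying by 1.2 under-allows for a 20% loss.

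A reader might go further and infer that the trial misses its planned power of 0.9. The documents do not support that. The fall to about 0.89 needs 30 to be exactly the 90% requirement in a two-sided pairwise test, and on the printed inputs no power is lost.

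**Conclusion.** The point holds as a minor arithmetic error. The 36 per group allows for 16.7% dropout, not the stated 20%; 20% would take 38 per group, or 114 in total. The expected shortfall against the plan's own requirement is 1.2 per group, assuming that dropout is counted among those enrolled and that those lost give no week-8 outcome. The protocol speaks of participants required and does not define them as participants with an observed outcome, so the shortfall is measured against the stated 30 and nothing stronger. No unconditional loss of power can be claimed.

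**What to change.** Keep 108 and correct one sentence in section 2.3: state either that 36 per group allows for about 16.7% dropout, or that about 29 per group are expected to remain if dropout reaches 20%. This changes nothing in the conduct of the trial; the only cost is a slightly less favourable stated margin.

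If the sponsor wants to keep both the 30 and the 20%, the matching enrolment is 38 per group, 114 in total. That is six more participants and 19 blocks of 6, which fits the block size in section 2.4; the total in the abstract would then change as well.

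Do not add a power of about 0.89 to the text, because it would rest on an effect size that the protocol does not state. If the base of 30 is re-derived, divide the new figure by 0.80 rather than multiplying by 1.2.
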